### 115 **Secondary Outcomes**

116

117 Secondary outcome measurements include the following:

118 1) 3-4 grade IVH

119 2) BPD

120 3) Mortality

121 Other secondary collected data will be:

122 1) Need for mechanical ventilation in the first 24 h of life

123 2) Peak hemoglobin level and hematocrit in the first 24 h of life

124 3) Need and number of blood transfusions

125 4) Need and duration of non invasive and invasive respiratory support

126 5) Use of inotropic drugs in the first 24 hours of life,

127 6) Cerebral oxygenation in the first 24 hours,

128 7) Superior vena cava blood flow in the first 24 hours.

129

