## 2.2 RATIONALE FOR PERFORMING THIS TRIAL

Based on these premises, we hypothesized that assisting preterm infants in the delivery room without clamping the umbilical cord at birth, thereby maintaining intact placental circulation, compared to assisting them after cord milking and early clamping, would result in better postnatal adaptation. This is demonstrated in the short term by a reduction in the need for mechanical ventilation within the first 24 hours, improved cerebral and intestinal hemodynamic parameters, and reduced use of plasma expanders or vasoactive drugs, and in the medium term by a reduction in severe complications such as severe cerebral haemorrhage, bronchopulmonary dysplasia, and mortality. The decision to compare assistance with intact placental circulation to assistance after cord milking, rather than to standard preterm infant care, which still does not widely include milking, is based on the positive scientific results published in favour of the latter procedure compared to standard care (i.e., immediate cord clamping without milking in infants with a gestational age of <30 weeks).

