## **3 POPULATIONS OF ANALYSIS**

The populations of analysis were not originally identified in the study protocol.

The primary and secondary efficacy analyses will be performed on the intention-to-treat (ITT) population. The same evaluations will be repeated on the per-protocol population, as sensitivity analyses.

The safety analyses will be performed on the safety population.

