### 3.4 SAFETY POPULATION

The safety population will include all randomized preterm infants who have received assistance according to one of the two interventional protocol procedures. Patients will be analysed according to type of assistance they received.

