## 4.2 SAFETY VARIABLES

Safety of the study interventional procedures will be evaluated by the following variables:

Intubation in delivery room  
Compressions in delivery room  
Use of i.v. adrenaline in delivery room  
Use of ET adrenaline in delivery room  
Use of surfactant in delivery room  
Total number of surfactant doses  
CRIB II score  
Max serum bilirubin  
Exchange transfusions  
Need of mechanical ventilation in the first 24 hours  
Duration of mechanical ventilation in the first 24 hours (hrs)  
Pharmacological closure of PDA  
Incidence of NEC  
Incidence of PLV  
Incidence of IVH  
Incidence of ROP  
Incidence of sepsis

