### 5.2.4 Safety Analyses

Data regarding the safety variables will be presented by treatment group and will be reported for the safety and PP populations. Evaluations on the PP population would be considered as sensitivity analyses.

The statistical analysis of the safety parameters will be conducted with the same approach adopted for the other secondary efficacy variable.

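### Need for mechanical ventilation in the first 24 h, a protocol secondary outcome, is reclassified as a safety variable without explanation and so has no ITT analysis

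*Combined protocol and SAP*

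**What the plan says.** The protocol's Secondary Outcomes section names the three components of the composite, then gives a second list of seven other secondary items. The first of the seven is "Need for mechanical ventilation in the first 24 h of life". SAP 2.2 sets out what better postnatal adaptation would look like and begins: "This is demonstrated in the short term by a reduction in the need for mechanical ventilation within the first 24 hours". It goes on to haemodynamic measures and the use of plasma expanders or vasoactive drugs.

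SAP 4.1.2, the list of secondary efficacy variables, does not contain this outcome. It appears in SAP 4.2 as "Need of mechanical ventilation in the first 24 hours", and its planned display, Table 6.10, is headed as a safety-population table.

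The list decides the population. SAP section 3 states: "The primary and secondary efficacy analyses will be performed on the intention-to-treat (ITT) population". For the other list it states: "The safety analyses will be performed on the safety population". SAP 3.4 defines that set: "The safety population will include all randomized preterm infants who have received assistance according to one of the two interventional protocol procedures". It then adds: "Patients will be analysed according to type of assistance they received". SAP 3.5 confirms that infants assisted with an off-protocol procedure are left out of the safety analyses. Under SAP 5.2.4 the safety variables "will be reported for the safety and PP populations"; ITT is not mentioned.

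**The concern.** An outcome that the protocol places among its secondary outcomes, and that the SAP's own rationale cites as a sign of benefit, would be compared only between groups that randomisation did not form. Under Study Procedures in the protocol, an infant in either arm whose assigned procedure is not performed, for a reason on the mother's or the infant's side, receives immediate clamping. That is neither study procedure, so the infant leaves the safety set. SAP 3.3 removes the same infant from the PP set, so neither planned analysis keeps the randomised groups intact.

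Early ventilation need is closely tied to the infant's condition at birth, which is also one of the reasons a procedure may be abandoned. If abandonment is more frequent in the PCI arm, removing those infants would make PCI look better than it is on this outcome.

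**Working it through.** The plan gives no figure for this outcome, so there is none to reproduce. The check has two parts.

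**1. Where each of the seven protocol items went**

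| Protocol item | SAP list | Population |
|---|---|---|
| 1. Mechanical ventilation need, first 24 h | 4.2 (Table 6.10) | Safety, PP |
| 2. Peak haemoglobin and haematocrit | 4.1.2 | ITT, PP |
| 3. Blood transfusions | 4.1.2 | ITT, PP |
| 4. Non-invasive and invasive respiratory support | 4.1.2 | ITT, PP |
| 5. Inotropes, first 24 h | 4.1.2 (dopamine, dobutamine) | ITT, PP |
| 6. Cerebral oxygenation | 4.1.2 (five time points) | ITT, PP |
| 7. Superior vena cava flow | 4.1.2 | ITT, PP |

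Only item 1 was moved. Neither document explains why.

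**2. How much the choice of population could matter**

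The documents give neither fallback rates nor a 24-h ventilation risk. Everything below is an assumption:

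- there is no true effect;
- each arm contains the same share *g* of fallback-type infants, as randomisation would give on average;
- the ventilation risk is *q* = 60% or 80% in fallback-type infants and *r* = 30% in the others;
- a share *e* of each arm falls back to immediate clamping and is excluded, with *e* = *g* in the PCI arm and *e* = 5% in the milking arm (UCM).

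Risk shown in the safety population: [(*g* − *e*)·*q* + (1 − *g*)·*r*] / (1 − *e*).

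Risk by ITT, the same in both arms: *g*·*q* + (1 − *g*)·*r*.

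In the PCI arm *e* = *g*, so the displayed risk is always *r* = 30.0%.

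| Fallback PCI / UCM | *q* | UCM shown | PCI lower by | ITT risk, both arms |
|---|---|---|---|---|
| 5% / 5% | 60% or 80% | 30.0% | 0 | 31.5% or 32.5% |
| 10% / 5% | 60% | (0.05×0.60 + 0.90×0.30)/0.95 = 31.6% | 1.6 points | 33.0% |
| 10% / 5% | 80% | (0.05×0.80 + 0.90×0.30)/0.95 = 32.6% | 2.6 points | 35.0% |
| 20% / 5% | 60% | (0.15×0.60 + 0.80×0.30)/0.95 = 34.7% | 4.7 points | 36.0% |
| 20% / 5% | 80% | (0.15×0.80 + 0.80×0.30)/0.95 = 37.9% | 7.9 points | 40.0% |

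The ITT difference is 0 in every row. If fallback were more frequent in the milking arm, the sign would reverse by symmetry.

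The table covers exclusions only. Regrouping of crossovers can be illustrated separately, again on assumed inputs: no true effect, 40% risk by ITT in both arms, and 10% of the PCI arm (risk 90%) not receiving PCI. The remaining PCI infants show (0.40 − 0.10×0.90)/0.90 = 34.4%.

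- If the 10% are excluded, the comparison is 34.4% versus 40.0%, an odds ratio of 0.79.
- If they are milked instead and counted there, milking shows (0.40 + 0.10×0.90)/1.10 = 44.5%, an odds ratio of 0.65.

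**The case against.** As-treated analysis is conventional for safety, and ventilation in the first day can be read as a harm measure as well as a benefit measure. That is a reason to keep Table 6.10, but not a reason to have no ITT analysis.

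Use and duration of invasive and non-invasive ventilation stay in SAP 4.1.2 under ITT (Tables 5.11–5.14). Invasive ventilation begun on day one would be counted there. This softens the loss, but those variables have no 24-h window and do not replace the named outcome. Tables 1.5 to 1.7 would also let a reader see who was excluded or not treated as assigned. That makes the problem visible without correcting it.

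The bias is not certain. Some procedures will be abandoned for maternal reasons, and SAP 2.5.2 reports that short cords could not be identified before randomisation, a possible cause of non-performance with no obvious link to ventilation need. The size depends almost entirely on the difference in fallback rates, which is unknown. This objection stands, and it is why the range above starts at zero.

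Three stronger readings are tempting and are not supported:

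- *That the SAP breaks an ITT commitment.* The protocol's Statistical Analysis section ties ITT only to the primary efficacy analysis, and SAP section 3 promises ITT only for variables it classes as efficacy. The defect is an unexplained change of class.
- *That this outcome is the SAP's proof of short-term benefit.* SAP 2.2 names it first among several signs, and the protocol places it below the three component outcomes.
- *That a key efficacy claim would rest on a non-randomised comparison.* The primary composite, its components and most secondary variables remain on ITT.

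**Conclusion.** The point holds as an unexplained reclassification with a consequence for the analysis. One of seven listed protocol secondary outcomes is moved to safety and thereby loses its ITT analysis, and both remaining analyses select infants on what happened after randomisation. The comparison could be biased, plausibly toward PCI. On the assumptions stated, the spurious difference runs from 0 (equal fallback) through 1.6–2.6 points (10% versus 5%) to 4.7–7.9 points (20% versus 5%). These are illustrations; the documents contain no adherence or event data that would narrow them. The primary analysis, the sample size and the type I error rate are unaffected. The change should be made, but it is not critical to the trial's main conclusion.

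**What to change.** Add need for mechanical ventilation in the first 24 h to SAP 4.1.2, with a Section 5 table on the ITT population and PP as the sensitivity analysis. Keep Table 6.10 as the supplementary as-treated display. Listing a variable in both places is already the SAP's practice: incidence of IVH appears in 4.1.2 and 4.2, with Tables 5.10 and 6.15.

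Two further changes are optional and would serve consistency only. Duration of ventilation within the first 24 h (Table 6.11) could be handled the same way, although the protocol does not name it as a secondary outcome. Pharmacological closure of PDA (Table 6.12) could be put on the same population as surgical treatment (Table 5.9); the protocol records both only under Further collected data.

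The cost is one list entry and one re-run of an existing table on the ITT flag. No new data are needed.

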## 4.3 HANDLING OF MISSING VALUES

Generally, subjects with missing value for a particular endpoint will contribute to the specific patient population and will be reported in all analyses as a special category ("missing value").

## 5 STATISTICAL AND ANALYTICAL METHODS

### 5.1 INTERIM ANALYSES, FINAL ANALYSES AND UNBLINDING

One *interim analysis* has been planned in the study protocol. However, the primary aim of this analysis was to evaluate the feasibility of the experimental intervention on a limited number of preterm infants and did not involve any of the primary and secondary

efficacy variables. For this reason, no one statistical procedure for the control of the type I error rate was adopted.

The *final analyses* will be performed after the official database release. The database will be locked at the end of all data entry and data cleaning procedures and when the patients' disposition in the study populations will be definitely defined in accordance with the study coordinator.

All statistical analyses will be performed with the statistical package SAS System 9.4.

Unblinding is not applicable to the present study.

## 5.2 STATISTICAL ANALYSES

Planned data display is reported in Appendix I. Tables referring to the PP population analyses have not been included in the data display since the PP analyses duplicate the ITT analyses on a different study population.

### 5.2.1 Patients' characteristics at baseline

Description of all baseline characteristics will be presented by interventional group. Data will be reported for the ITT and PP populations.

Discrete variables will be summarized by frequencies and percentages. Percentages will be calculated according to the total number of patients assigned to each interventional group and to the total number of patients included in the specific analysis population.

Continuous variables will be summarized by use of standard measures of central tendency and dispersion: mean, standard deviation (SD), standard error (SE), median, minimum, maximum, interquartile range (IQR).

No formal test will be performed to compare patients' characteristics at baseline.

### 5.2.2 Primary efficacy analysis

Data regarding the primary efficacy variable will be presented by treatment group and will be reported for the ITT and PP populations. Evaluations on the PP population would be considered as sensitivity analyses.

The distribution of patients by the incidence of composite endpoint will be summarized by frequencies and percentages. Percentages will be calculated according to the total number of patients assigned to each interventional group and to the total number of patients included in the specific analysis population. The 95% CI of the percentage will be calculated according to the exact method.

The proportions of events occurred in the two interventional arms will be compared with the chi-square test for heterogeneity or the Fisher's exact test, if appropriate.

The estimate of the odds ratio and its 95% Wald CI will be obtained with a logistic regression model with the interventional arm as independent covariate. The umbilical

cord milking arm will be treated as reference group. The Wald chi-square test will be used to test the effect of the experimental intervention.

With the intent to verify if a heterogeneity of the experimental treatment effect exists in strata identify by gestational age (23-26 wks. versus 27-29 wks.) and type of delivery (vaginal versus caesarean), two subgroup analyses will be performed with a logistic regression model including the interventional group, the stratification variable, and their interaction term. The odds ratios of event and their 95% Wald CI will be estimated in each stratum and the interaction test will be used to test the heterogeneity of the strata-specific treatment effects.

No adjustment for multiplicity will be adopted.

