### 150 **Sample Size Calculation**

151 The frequency of the composite primary outcome in the participating Italian neonatal units is about  
152 47% (severe IVH 8.0%, BPD 24.4%, mortality 14.6%). Meta-analyses showed a reduction of 32%  
153 in in-hospital mortality and of 17% in any IVH in preterm infants assisted at birth with delayed cord

154 clamping instead of immediate cord clamping (6;24). Moreover, no data on the incidence of  
155 outcomes between UCM and delayed cord clamping is available. Thus, we arbitrarily hypothesized  
156 that neonatal assistance with PCI might decrease the frequency of the composite primary outcome  
157 from 47% to 28%. Considering a dropout rate of 5%, we calculated that 106 newborns must be  
158 enrolled in each group to detect this difference as statistically significant with 80% power at a level  
159 of 0.05 using a 2-sided chi-square test.

160

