## 161 **TREATMENT OF SUBJECTS**

### 162 **Randomization**

163 Infants at each unit are randomly assigned in blocks to a treatment group (PCI or UCM) in a 1:1  
164 ratio. The allocation sequences consist of computer generated random numbers. Since the  
165 frequency of the composite primary outcome is inversely related to gestational age, the inclusion  
166 of patients is balanced in each treatment group according to the following gestational ages: 23+0  
167 to 26+6 weeks or 27+0 to 29+6 weeks.

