## 2.7 SAMPLE SIZE

Assuming a proportion of events (grade 3 or 4 IVH, moderate or severe BPD or death from any cause) equal to 47% in the control arm and equal or less than 28% in the experimental arm, corresponding to a relative reduction of the unfavourable events equal to 40%, it was calculated that a sample size of 200 preterm infants (100 per group) would have guaranteed a study power equal to 80%, with a two-sided alpha error equal to 5%, for a standard chi-square test for heterogeneity.

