## 2.8 TREATMENT ALLOCATION

Assignment of each preterm infant to one of the two interventional groups has been performed using a minimization algorithm, with an allocation ratio equal to 1:1.

Minimization is a dynamic randomization algorithm designed to minimize imbalance between treatments taking stratification factors into account. Based on characteristics of

the current patient and treatment assignments and characteristics of enrolled patients an imbalance score is computed. In the present study, the assignment was performed using a randomization list with an allocation ratio equal to 1:1 in absence of imbalance. A random component in intervention selection was also used in case of imbalance. Indeed, in this situation, a randomization list with an allocation ratio equal to 1:5 in favour of the intervention with the highest imbalance score was used.

The gestational age (23+0 to 26+6 versus 27+0 to 29+6) has been used as a stratification factor.

Treatment allocation process has been carried out at all participating centres by a restricted access web-based system (<https://www.eclintrials.org/ect>), administered by the Clinical Epidemiology Unit of the IRCCS Ospedale Policlinico San Martino, Genoa, Italy, active 24-hour, and 365 days a year.

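### The primary analysis leaves out gestational age, the factor allocation was balanced on, so it is somewhat conservative and forgoes power that a stratified test would give

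*Combined protocol and SAP*

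**What the plan says.** **Allocation.** SAP 2.8 says infants were assigned "using a minimization algorithm, with an allocation ratio equal to 1:1", and names one balancing factor: "The gestational age (23+0 to 26+6 versus 27+0 to 29+6) has been used as a stratification factor". The protocol's Randomization section gives the reason: "frequency of the composite primary outcome is inversely related to gestational age, the inclusion" (the sentence goes on to say that enrolment is balanced between arms in two gestational-age bands).

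**Primary analysis.** SAP 5.2.2 compares the two proportions with a chi-square test, or Fisher's test where appropriate. The odds ratio and its Wald interval come from a "logistic regression model with the interventional arm as independent covariate", with a Wald test of the same effect. Gestational age enters only through a subgroup model with an interaction term. Appendix 1, note 2, adds a crude difference in proportions with an exact interval. The protocol's Statistical Analysis section plans univariate tests and an odds ratio only.

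**Scope.** SAP 5.2.3 carries the approach of 5.2.2 over to the three components, and the per-protocol analyses repeat it. No overall treatment effect adjusted for or stratified by gestational age is planned, even as a sensitivity analysis.

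**The concern.** Balancing the arms on a prognostic factor removes between-stratum variation from the comparison. An arm-only analysis still counts that variation in its standard error, so the stated uncertainty of the crude effect exceeds the real one. The test then rejects too rarely under the null, and its interval over-covers.

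The stake is efficiency. The trial was sized for about 80% power against an effect that the protocol itself describes as arbitrarily chosen. If the true effect is smaller, power is lower, and any power that can be had without further infants is worth taking. The stratum is already recorded for allocation and tabulated in SAP Table 2.3.

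**Working it through.** **1. The plan's own figure.** SAP 2.7 assumes event proportions "equal to 47% in the control arm and equal or less than 28% in the experimental arm", 100 per arm, 80% power and two-sided 5%. With the pooled-variance formula and mean risk 0.375:

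n = [1.960·√(2·0.375·0.625) + 0.842·√(0.47·0.53 + 0.28·0.72)]² / 0.19² = (1.342 + 0.565)² / 0.0361 ≈ 100.7, so 101 per arm.

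Power at exactly 100 per arm is 79.7%. For dropout the protocol says "Considering a dropout rate of 5%, we calculated that 106 newborns must be" enrolled in each group; 100/0.95 = 105.3, which rounds up to 106. The figures reproduce, and they are for the unadjusted chi-square test.

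**2. Assumptions for the rest.** The documents give neither the share of infants at 23-26 weeks nor the risk in each stratum. I assume a 40% share, overall risks of 47% and 28%, a common odds ratio across strata, 100 per arm and balance within strata. The control-risk gap g between strata varies from 0 to 47 points.

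**3. Why the crude test is conservative.** In an arm with risk 47% the crude variance term is 0.47·0.53 = 0.2491. The part due to the strata is 0.4·0.6·g². At g = 0.40 this is 0.0384, leaving 0.2107 within strata. The true standard error is then √(0.2107/0.2491) = 0.920 of the one used. The effective critical value is 1.96/0.920 = 2.13, a two-sided error of about 3.3%. Simulation gives slightly more (3.8%), because the uncorrected chi-square at this sample size runs at about 5.6% when there is no gap.

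**4. Simulation, chi-square versus Cochran-Mantel-Haenszel (CMH).**

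| Control-risk gap | Type I error, crude / CMH | Power, crude / CMH | Gain (points) |
|---|---|---|---|
| 0 | 5.6% / 5.6% | 80% / 80% | 0 |
| 20 points | 5.0% / 5.1% | 80.0% / 80.8% | 0.8 |
| 30 points | 4.6% / 4.9% | 80.8% / 83.2% | 2.4 |
| 40 points | 3.8% / 5.1% | 81.7% / 85.8% | 4.1 |
| 47 points | 3.1% / 4.9% | 82.4% / 88.0% | 5.6 |

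Shares of 35% and 50% give nearly the same picture. Replacing exact balance by a 5/6 biased coin within strata, taken to favour the under-represented arm, also changes little: at 40 points, 3.9% / 5.1% and 81.7% / 85.7%.

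**5. What happens to the intervals (40-point gap).**

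- *Crude odds ratio* (35% share): mean model standard error of the log odds ratio 0.302, true sampling SD 0.282, coverage of the nominal 95% interval 96.6%.
- *Logistic model with arm plus stratum* (35% share): the standard error rises to 0.334, while the odds ratio moves from 0.44 to 0.38. The ratio of mean estimate to standard error goes from 0.833/0.302 = 2.76 to 0.989/0.334 = 2.96. The power comes from that shift, not from a narrower interval.
- *Risk difference* (40% share): the control risks are 71% and 31%, and a common odds ratio of 0.38 gives experimental risks of 48.2% and 14.6%. The crude standard error is √(0.4507/100) = 0.0671. The stratified one is √{[0.4·(0.71·0.29 + 0.482·0.518) + 0.6·(0.31·0.69 + 0.146·0.854)]/100} = √(0.3854/100) = 0.0621. The 95% half-width falls from 13.2 to 12.2 percentage points. This interval does narrow.

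**The case against.** The test and the sample size agree with each other: both are for an unadjusted chi-square, and it delivers the planned power in every scenario. The gain rests on stratum figures that the documents do not give, and it is negligible at a gap of 20 points or less. The SAP also reports stratum-specific odds ratios, an interaction test and counts by arm within each stratum (Tables 3.3 and 3.4), so a reader could compute a stratified estimate. All of this stands, and it limits the point to a recommendation. It does not replace a pre-specified overall stratified effect.

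Achieved balance is also unverified. The protocol describes blocks within units and the SAP minimisation with a random element. The SAP's wording on which arm its 1:5 list favours is unclear.

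A reader might draw three stronger conclusions, none of them supported:

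- *That the type I error is not controlled.* It is at or below the level of the stratified test, apart from simulation noise. False positives are not inflated by the omission.
- *That the trial becomes underpowered.* The loss is only relative to what a stratified analysis would achieve.
- *That adding gestational age to the logistic model tightens the odds ratio's interval, or changes the odds ratio only slightly.* With control risks of 75% and 28%, the odds ratio moves from 0.44 to about 0.36 and its upper-to-lower limit ratio widens from 3.24 to 3.83. It is a different, conditional quantity.

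SAP 5.2.2 also does not say whether the chi-square/Fisher or the Wald test decides. Since SAP 2.7 sizes the trial on the chi-square, that test can be inferred, but naming one would be cleaner.

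**Conclusion.** The point holds as an efficiency improvement. The plan balances on gestational age because it predicts the outcome, then leaves it out of the overall primary comparison. Given balance within strata, the crude test is conservative and the crude intervals over-cover. The power forgone runs from nothing (no gap) to between 5 and 6 points (47-point gap), and unadjusted type I error falls to about 3% at the top of that range.

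The direction follows from the design. The size rests on the assumed 40% share, the assumed gaps, a common odds ratio and achieved balance. The planned analysis remains valid and meets its stated power, so the change is recommended rather than required.

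**What to change.** In SAP 5.2.2:

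- Name one primary test: Cochran-Mantel-Haenszel, stratified by gestational age (23+0-26+6 and 27+0-29+6).
- Make a stratified or standardised risk difference, with its 95% interval, the main effect estimate, and give the risk ratio beside it.
- If an odds ratio from a logistic model with arm plus stratum is reported, label it conditional. State that it lies further from 1 and has a larger standard error than the crude odds ratio.
- Keep the crude chi-square test and crude odds ratio as supportive analyses.
- Apply the same approach to the three components and to the per-protocol analysis.
- Confirm the allocation method and tabulate achieved balance within strata.

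The cost is small: a few sentences of SAP text and minor programming, with no new data. The primary test would differ from the one used for the sample size, and the conditional and crude odds ratios must be kept apart in reporting. Because SAP 2.4 describes enrolment as complete, the change should be dated and made before database lock, by a statistician still blind to allocation and results.
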